#### Secondary outcomes

2.8.2

##### Refill and medication adherence scales

2.8.2.1

The scale has two dimensions: medication adherence and medication refilling (55). Medication adherence includes four items, while medication refilling includes three, for a total of seven items. Participants were scored on a 4-point Likert scale, ranging from “never” to “all the time.” The 7th question was a reverse question setting, with a total score of 7–28. A lower score indicates better adherence. The scale is as follows: Question 1: How often do you forget to take your medication? Question 2: How often do you decide not to take your medication? Question 3: How often do you forget to fill your prescription? Question 4: How often do you still need to take your medication but do not have it on hand? Question 5: How often do you miss taking your medication when you are feeling better? Question 6: How often do you miss taking your medication when you are not feeling well? Question 7: How often do you plan ahead and refill your medications before they run out? The ARMS is a valid and reliable self-report measure of medication adherence. The Chinese version of the ARMS scale demonstrates good internal consistency reliability (Cronbach’s *α* = 0.731) (56).

##### Quality of life, EQ-5D-5L

2.8.2.2

The EQ-5D-5L is an enhanced version of the EQ-5D, adding five additional levels to the original five dimensions for a more refined health status assessment. The EQ-5D-5L scale consists of two parts, the five-dimensional description and the visual analogue score. The five-dimensional description includes five dimensions: mobility, self-care, daily activities, pain or discomfort, and anxiety or frustration. Each dimension has five levels of difficulty: no difficulty, little difficulty, moderate difficulty, great difficulty, and complete difficulty. The visual analogue score measures overall health on a scale from 0 to 100, with higher scores indicating better health. The visual analogue scale is a vertical scale, with a top score of 100 for “best health” and a bottom score of 0 for “worst health.” It provides a continuous variable for measuring overall quality of life. The Cronbach’s *α* coefficient of this scale is 0.857 (57).

##### Anxiety depression ultra short form, PHQ-4

2.8.2.3

The PHQ-4 is a simplified version of the Anxiety and Depression Scale, with two dimensions: depression and anxiety. It consists of four entries, which are scored on a Likert 4 scale (1 = not at all, 2 = for a few days, 3 = for more than half of the days, and 4 = almost every day). Participants are required to assess their experiences of anxiety and depression using this scale. The total score ranges from 4 to 16, with higher scores indicating more severe anxiety and depression symptoms. This concise and easy to understand scale enables medical staff to quickly identify patients with anxiety and depression symptoms and provide an initial assessment. The PHQ-4 has a Cronbach’s *α* of 0.82, demonstrating good internal consistency (58).

##### Perceived stress scale, PSS-4

2.8.2.4

The Perceived Stress Scale (PSS) is one of the most widely used tools in the world for measuring psychological stress. Developed by Cohen et al., the original version contained 14 entries (PSS-14), consisting of seven negatively descriptive and seven positively descriptive items. Instead of focusing on specific events, the PSS assesses the degree to which participants perceive their lives as unpredictable, uncontrollable, or overloaded. Each item is scored on a scale of 0–4, with higher scores reflecting greater perceived stress. To create shorter versions, Cohen et al. selected entries from the PSS-14, resulting in the PSS-10 and PSS-4, respectively. For the total scale score, scores of the positive items were reversed and all item scores were summed, with higher scores indicating higher perceived stress. In this study, the PSS-4 was used to evaluate stress trends, with a Cronbach’s *α* coefficient of 0.75 for the items (59).

##### Perceived social support scale, PSSS-12

2.8.2.5

The scale developed by Zimet et al. (75) consists of three dimensions: family support, friend support, and other support. Each dimension contains four entries, making a total of 12 entries. Participants were rated on a 7-point Likert scale from “strongly disagree” to “strongly agree,” with scores ranging from 12 to 84. A higher total score indicates a higher level of perceived social support. The scale categorizes the level of perceived support into three categories: low (12–36 points), intermediate (37–60 points), and high (61–84 points). The original scale was initially used with American college students and has since been translated into multiple languages for widespread use in various countries. The translations have shown good reliability, with an internal consistency coefficient of 0.93 (59). Furthermore, the scale has been used in studies on perceived social support and psychological resilience in patients with ischemic stroke and coronary heart disease.

##### Customer satisfaction questionnaire (CSQ-3)

2.8.2.6

The CSQ is a widely used questionnaire for assessing user satisfaction with telemedicine services. This is likely because the CSQ measures various attributes, including the physical environment, procedures, facilitators, service type, treatment staff, service volume or duration, service quality, outcomes, and overall satisfaction. The scale consists of three items, each rated from 1 (low satisfaction) to 4 (high satisfaction). Higher total scores indicate better satisfaction. The Cronbach’s alpha coefficient for the scale is 0.87, indicating good validity both overall and for each component (60).

### Statistical analysis

2.9

Statistical analyses will be performed using SPSS Statistics 26.0 software. Count data will be expressed as the number of cases and rate (%), while measurement data will be presented as mean ± standard deviation. Before performing parametric tests, normality assumptions will be tested using the Shapiro–Wilk test. If data is normally distributed, parametric tests, such as the independent *t*-test, may be used. However, if the normality assumption is violated, non-parametric tests, such as the Mann–Whitney U test, will be used to compare changes in scale scores between baseline and endpoint between the two groups. The Wilcoxon signed-rank test will be employed for within-group comparisons of scale scores between baseline and endpoint. Demographic and clinical characteristics at baseline will be summarized descriptively for each group. Categorical variables will be reported as counts and percentages, and continuous variables as mean ± standard deviation.

For the primary analysis, all randomized participants will be included in an intention-to-treat (ITT) analysis, regardless of whether they complete the intervention. For secondary analyses, only participants who complete the intervention and follow-up will be included in a per-protocol (PP) analysis.

Regarding missing data, we will explore the missing data and compare the distribution of key variables. If the missing data is reasonable in amount and assumed to be Missing at Random (MAR), multiple imputation methods will be used to handle the missing data for both ITT and PP analyses. This ensures that the handling of missing data is consistent across both analysis groups. Baseline variables will be used as auxiliary variables for imputation, and multiple imputed datasets will be generated. Linear regression and logistic regression will be applied to analyze the imputed datasets, and the results will be pooled to provide final estimates and standard errors. A two-sided test will be used, and statistical significance will be defined as *p* < 0.05. The detailed statistical analysis plan for this study is available for public access at the Chinese Clinical Trial Registry: ChiCTR Statistical Analysis Plan (https://www.chictr.org.cn/showproj.html?proj=196659).

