#### Primary outcome

2.8.1

The primary outcome is the proportion of individuals adopting health behaviors and knowing rate of health knowledge.

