##### Proportion of individuals adopting health behaviors

2.8.1.1

The health behavior was assessed using a self-designed health behavior scale, which consists of five domains: (1) frequency of personal protective measures during contact with livestock (5 items), (2) frequency of personal protective measures when handling lambs and aborted materials (5 items), (3) frequency of personal protective measures when vaccinating livestock (5 items), (4) frequency of cleaning measures when cleaning animal pens (3 items), and (5) frequency of hand hygiene maintenance after contact with cattle, sheep, their placental tissues, or meat products (4 items). Each item was rated on a 5-point Likert scale: “Never (0),” “Rarely (1),” “Sometimes (2),” “Often (3),” and “Almost Always (4).” One reverse-scored item was included in each domain. The total score ranges from 0 to 110, with higher scores indicating better health behavior.

This scale was developed to evaluate the frequency of health behaviors related to occupational safety and hygiene practices among individuals at risk for brucellosis.

The proportion of individuals adopting health behaviors is calculated by determining the proportion of participants who meet the health behavior standard, as assessed by the health behavior questionnaire. A threshold score will be established to determine whether an individual has adopted health behaviors, with a score above 70 considered indicative of good health behavior formation. The adopting proportion is then calculated by dividing the number of individuals exceeding this threshold by the total number of participants.

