##### Knowing rate of health knowledge

2.8.1.2

The Brucellosis Health Knowledge Awareness questionnaire was designed based on the “National Brucellosis Surveillance Program” and tailored to the specific context of Baoding City, Hebei Province. The questionnaire includes items on awareness of brucellosis, its clinical symptoms, and modes of transmission. Participants indicated their knowledge, with correct answers marked as “aware” and incorrect or unknown answers as “unaware.”

The awareness rate for each item was calculated as the number of correct responses divided by the total number of valid respondents, multiplied by 100%. The overall knowledge awareness rate was calculated by dividing the total number of correct responses by the product of the total number of respondents and the total number of questions, then multiplying by 100%.

This questionnaire assesses health knowledge about brucellosis within the local population, providing essential information for health interventions.

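### The explicit between-group tests compare changes in scale scores, not the yes/no primary outcome, and regression is named only for imputed data and tied to no outcome

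*Protocol article*

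**What the plan says.** Section 2.8.1 (Primary outcome) names two primaries: "The primary outcome is the proportion of individuals adopting health behaviors and knowing rate of health knowledge". Section 2.8.1.1 makes the first one binary for each patient, "with a score above 70 considered indicative of good health behavior formation", and forms the group figure by "dividing the number of individuals exceeding this threshold by the total number of participants". Section 2.4 (Sample size) is built on this proportion, at 90% against 60%. Section 2.8.1.2 marks each answer as aware or unaware and then defines the overall knowledge rate by "dividing the total number of correct responses by the product of the total number of respondents and the total number of questions".

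Section 2.9 gives the analysis. First, "normality assumptions will be tested using the Shapiro–Wilk test". With normal data a parametric test such as the independent t-test may be used; otherwise non-parametric tests such as the Mann–Whitney U test "will be used to compare changes in scale scores between baseline and endpoint between the two groups". It adds: "The Wilcoxon signed-rank test will be employed for within-group comparisons of scale scores between baseline and endpoint". The primary analysis is intention-to-treat. If the amount of missing data is acceptable and can be taken as missing at random, multiple imputation is used, with baseline variables as auxiliaries, and then "Linear regression and logistic regression will be applied to analyze the imputed datasets", with results pooled.

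Table 1 shows every outcome except satisfaction measured at month 0 as well as at months 3, 6, 9 and 12.

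**The concern.** The only group comparisons described without reference to imputation concern changes in scale scores. A change in behaviour score is a different quantity from the proportion above 70, so these tests do not answer the question the trial was sized for. The method that would answer it, logistic regression, appears only in the missing-data paragraph, with no outcome attached. A reader cannot tell whether the headline result will be a pre-tested two-sample comparison of change or a pooled regression, and the choice turns on how much data are missing. That leaves room to choose after the results are seen.

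The change-score choice also discards precision on the continuous scores in a trial planned for 58 patients. The within-group signed-rank tests do not address the difference between arms, which is the hypothesis in sections 1 and 2.1.

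**Working it through.** **1. The plan's own figure.** Section 2.4 gives 23 per arm for 90% against 60%, raised for 20% loss: 23 / 0.8 = 28.75, so 29 per arm and 58 in total. The inflation reproduces. The 23 does not follow from two-sided α = 0.05 with 80% or 90% power (pooled formula: 32 and 42 per arm). That is a separate matter. What counts here is that the calculation compares two proportions.

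**2. Outcomes set against methods in section 2.9.**

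| Outcome | Type | Described without imputation | Described for imputed data |
|---|---|---|---|
| Adopter status (first primary) | yes/no | no test of proportions named | logistic regression would fit, not assigned |
| Knowledge rate (second primary) | group rate as written | t-test or Mann–Whitney fits only if a per-patient score is derived | linear regression would fit, not assigned |
| Other scales | continuous | t-test or Mann–Whitney on change | linear regression would fit, not assigned |

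The missing test for the first primary has practical weight. By exact enumeration at 90% against 60%, two-sided 0.05, the unadjusted chi-square test has power 69% at 23 per arm and 78% at 29; Fisher's exact test has 57% and 68%.

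**3. Knowledge.** Let patient i answer cᵢ of Q questions correctly. The stated rate is Σcᵢ / (N × Q). If everyone answers every question, this equals the mean over patients of cᵢ / Q. A per-patient percent correct therefore reproduces the plan's rate and can be analysed with the patient as the unit.

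**4. Change score against baseline adjustment (continuous scores only).** Assume equal variance σ² at baseline and endpoint, and correlation ρ in both arms. The documents give neither an SD nor ρ, so a range is shown.

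- Variance of change: 2σ²(1 − ρ)
- Residual variance after baseline adjustment (ANCOVA): σ²(1 − ρ²)
- Ratio: (1 − ρ²) / [2(1 − ρ)] = (1 + ρ)/2

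| ρ | Change (σ² = 1) | ANCOVA | Ratio | Extra patients change scores need (1/ratio − 1) |
|---|---|---|---|---|
| 0.3 | 1.40 | 0.91 | 0.65 | 54% |
| 0.5 | 1.00 | 0.75 | 0.75 | 33% |
| 0.7 | 0.60 | 0.51 | 0.85 | 18% |

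As an illustration, for an assumed difference of 0.75 SD with 29 per arm, power for change score and ANCOVA is 67% and 85% (ρ = 0.3), 81% and 91% (ρ = 0.5), 96% and 98% (ρ = 0.7).

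**5. Can a logistic model be fitted?** With 29 per arm at the planned rates, expected non-adopters are 0.1 × 29 = 2.9 and 0.4 × 29 = 11.6, about 14 to 15 in all. That is enough for arm plus one covariate. The chance of no non-adopter in the intervention arm is 0.9²⁹ ≈ 5% (0.9²³ ≈ 9% with 23). In that case ordinary logistic regression fails through separation, so a fallback is needed.

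**The case against.** The strongest reply is that section 2.9 does name a suitable method. The primary analysis is intention-to-treat, 20% loss is expected, imputation is the planned response, and logistic regression fits a yes/no outcome. On that reading pooled regression is the probable primary result, and the two-sample tests are only examples. The section also cites a detailed analysis plan that is not shown, where covariates and the assignment of outcomes to models would normally stand. This carries weight: the absence of a covariate list is not held against the article. What stands is that the text describes two kinds of between-group analysis, makes regression conditional on imputation, and ties neither primary to it.

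Several stronger readings are tempting but not supported:

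- **That no named method fits either primary.** Logistic regression fits the first, and the aware/unaware marking lets a per-patient percent correct be derived for the second.
- **That pooled knowledge answers will be tested as independent, inflating type I error.** No section plans this; section 2.8.1.2 gives a descriptive formula.
- **That baseline enters only through change scores.** Section 2.9 also uses baseline variables as imputation auxiliaries.
- **That change scores bias the comparison.** Under randomisation they do not; the loss is precision.
- **That rank tests are to be pooled over imputations, or within-group tests read as proof of effect.** The plan says neither.

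**Conclusion.** The point holds in limited form and should be settled before analysis. The explicit between-group tests address changes in scale scores, whereas the first primary outcome and the sample size rest on a proportion. Regression, which would serve all the outcomes, is confined to imputed data and assigned to none, so the analysis that is read depends on whether imputation is done.

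The measurable part is efficiency on continuous scores: baseline adjustment has 0.65, 0.75 or 0.85 of the change-score variance at ρ of 0.3, 0.5 or 0.7. This rests on assumed correlations and equal variances, and on no figure from the documents. It covers knowledge only if that is scored per patient, together with the secondary scales. It must not be read as a gain for the yes/no primary. The unseen analysis plan may already resolve the assignment of models; if so, the article should be brought into line with it.

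**What to change.** Make regression the single between-group analysis, whether or not data are imputed:

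- **Adopter status:** logistic regression on arm plus the continuous month-0 behaviour score, with a penalised fit (for example Firth) stated in advance for the case of separation.
- **Knowledge:** define each patient's percent correct and use linear regression on arm plus its month-0 value.
- **Every other scale with a month-0 value:** linear regression on arm plus baseline, with robust or bootstrap standard errors if skewed.
- **Remove** the Shapiro–Wilk gate, and keep the within-group signed-rank tests as descriptive only.

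No new data are needed, since Table 1 already collects every baseline value used, and both regression types are already named in section 2.9. The cost is a change of wording and slightly more analysis work. It should be checked whether SPSS 26.0 can run the penalised fit on imputed data or whether other software is needed.

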## Discussion

3

The use of mHealth in patient care has grown significantly since the COVID-19 outbreak, further accelerated by the World Health Organization’s call to expand the use of digital technologies to enhance remote care and support for patients (61). The rise of mHealth has proven to complement traditional clinical care effectively (62). Relevant studies have shown that mHealth plays a crucial role in improving patient adherence and enhancing acceptability, feasibility, and efficiency in brucellosis treatment (63). Brucellosis, a zoonotic disease endemic in the Middle East and present in regions such as China, Africa, and others (64), is classified as a re-emerging and neglected disease (65–68). In humans, the disease may cause mild symptoms, but it can also lead to more severe or chronic conditions. The disease is transmitted to humans through direct contact with tissues or blood from infected animals or through the consumption of contaminated animal products, including unpasteurized milk and cheese. Transmission via gas solvent may also occur (69–71). Although no human vaccine is currently available (72), efforts are underway to develop one (73). However, vaccines for animals are available. To prevent infection, individuals should avoid contact with infected animals or their products. Human behavior is critical in the control and prevention of brucellosis. Developing personal skills is based on the idea that individuals should be provided with the information and skills to take control of their health, develop strategies to combat the disease, and change norms to create a social environment that promotes health and prevention of brucellosis. Despite evidence suggesting that health promotion interventions grounded in behavioral science theories are more effective than those without such frameworks, few studies on brucellosis self-management have used theoretical models as a guide. Therefore, this study aims to evaluate an mHealth intervention based on the HAPA model to enhance self-management among individuals with brucellosis. Engaging in self-management behaviors is believed to influence both proximal health outcomes and distal outcomes of health status improvement (74). HAPA summarizes the key components of the health behavior change process and provides essential guidelines for intervention development, which is crucial for designing the interventions in this study. This study will be the first health intervention research in China to apply the HAPA theoretical model as a guide for managing brucellosis patients. The purpose of this study is to assess the effectiveness of the HAPA model as a theoretical guide for improving health behaviors in brucellosis patients and to validate its utility as an effective framework for guiding behavior change. This study will help address the research gap in postoperative health management for brucellosis patients in China, guided by health theory. To more comprehensively capture the impact of the intervention, the results and discussion will not only compare outcomes between the intervention and control groups, but will also include a longitudinal analysis across different time points during the study, enabling a more detailed understanding of behavioral changes over time.

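### Section 2.9 names only baseline variables for imputation, leaves the endpoint undated and gives no method for the promised longitudinal analysis, although both primary outcomes are also collected at Months 3, 6 and 9

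*Protocol article*

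**What the plan says.** All of the following is in the protocol article.

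- **Missing data (section 2.9).** Imputation is conditional: "If the missing data is reasonable in amount and assumed to be Missing at Random (MAR), multiple imputation methods will be used". The predictors are described in one sentence: "Baseline variables will be used as auxiliary variables for imputation, and multiple imputed datasets will be generated". After that, "Linear regression and logistic regression will be applied to analyze the imputed datasets" and the results are pooled.
- **Tests (section 2.9).** The between-group tests "will be used to compare changes in scale scores between baseline and endpoint between the two groups". Within groups, "The Wilcoxon signed-rank test will be employed for within-group comparisons of scale scores between baseline and endpoint". The endpoint is given no month, and no repeated-measures method is named.
- **Schedule (Table 1).** Both primary outcomes, health-behaviour adoption and health knowledge, are marked at Months 0, 3, 6, 9 and 12. Section 2.1 also describes questionnaires at the start and at three-month intervals, which are then analysed.
- **Discussion (section 3).** The results "will also include a longitudinal analysis across different time points during the study".
- **Expected loss (section 2.4).** 20% of participants, with 29 randomised per group.

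**The concern.** A participant's Month 3, 6 and 9 scores will usually predict a missing Month 12 score better than baseline does. They may also be related to why the participant left. If dropout depends on how someone was doing after the intervention, the missing-at-random assumption holds only once those scores are conditioned on. A model built from baseline alone then fills the gaps as if dropouts had fared like completers with the same baseline. If dropout works differently by arm, the error does not cancel and falls on the estimated effect. This is plausible here, because only one arm gets intensive WeChat contact, for three months, and Table 1 follows participants to Month 12.

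Separately, section 2.9 and the Discussion do not match. One describes baseline-to-endpoint tests; the other commits to an analysis over time with no stated model. Without an endpoint month, a reader cannot tell which visits precede the endpoint and could inform the imputation.

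**Working it through.** **1. The plan's own figure for loss.** Section 2.4: 23 / (1 − 0.20) = 28.75, rounded up to 29 per group. The inflation step reproduces. The expected loss is 0.20 × 29 = 5.8, or about 6 per arm.

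**2. How the bias arises.** In one arm, with missing fraction f:

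bias of arm mean = f × average among dropouts of (imputed value − true value)

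bias of group difference = intervention-arm bias − control-arm bias

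If dropout has the same rate in both arms and depends in the same way on the score relative to the arm's own mean, the two terms are equal and cancel.

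**3. Size under stated assumptions.** The documents give no correlations and no dropout mechanism, so these inputs are assumed:

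- endpoint at Month 12 and a true difference of 0.50 SD
- 20% loss in each arm (rate from section 2.4), all of it after Month 9
- dropout driven by low Month 9 scores in the intervention arm only, with log-odds of 0.5, 1 or 2 per SD
- correlation 0.3, 0.5 or 0.7, either AR(1) (decaying with distance between visits) or exchangeable.

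Large-sample simulation (200,000 per arm), estimated difference in SD with baseline-only imputation:

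| Correlation | Log-odds 0.5 | Log-odds 1 | Log-odds 2 |
|---|---|---|---|
| AR(1) 0.3 | 0.530 | 0.552 | 0.577 |
| AR(1) 0.5 | 0.544 | 0.583 | 0.627 |
| AR(1) 0.7 | 0.560 | 0.605 | 0.668 |
| Exchangeable 0.3 | 0.517 | 0.539 | 0.561 |
| Exchangeable 0.5 | 0.524 | 0.545 | 0.574 |
| Exchangeable 0.7 | 0.523 | 0.542 | 0.564 |

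The bias runs from 0.517 − 0.50 = 0.017 to 0.668 − 0.50 = 0.168, about +0.02 to +0.17 SD. With Months 3, 6 and 9 added, every scenario gives 0.496 to 0.505, so the bias is gone.

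When the dropout mechanism was made the same in both arms, baseline-only imputation showed no bias in the mean difference.

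**4. Precision.** With 20% missing, the variance of an arm mean relative to complete data is about

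1 + (0.20 / 0.80) × (1 − R²) = 1 + 0.25 × (1 − R²),

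where R² is the share of Month 12 variance that the predictors explain. The formula is approximate when dropout depends on scores.

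| Correlation | R², baseline only | Factor | R², Months 3–9 added | Factor |
|---|---|---|---|---|
| AR(1) 0.3 | 0.000 | 1.25 | 0.090 | 1.23 |
| AR(1) 0.7 | 0.058 | 1.24 | 0.490 | 1.13 |
| Exchangeable 0.5 | 0.250 | 1.19 | 0.400 | 1.15 |
| Exchangeable 0.7 | 0.490 | 1.13 | 0.632 | 1.09 |

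In these rows the variance falls by about 2% (1.2275/1.25 = 0.98) to 9% (1.1275/1.2355 = 0.91). This is a best case, because participants lost before Month 9 do not supply all the interim scores.

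**5. Against sampling error.** With 23 evaluable per arm, the standard error of a standardised difference is about √(2/23) = 0.29 SD. The largest bias is 0.17/0.29, or about 0.6 of a standard error; the smallest is 0.02/0.29, or about 0.07.

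**The case against.** The strongest reply is that the text nowhere excludes post-baseline variables. Auxiliary variables are by definition additional to the analysis variables, so arm and the analysed outcome would be in the model anyway. The full predictor list may also be in the analysis plan that section 2.9 refers to, which is not shown. This stands in part: baseline variables are the only ones named, but exclusivity is an inference. Interim scores count as analysis variables only if the analysis is longitudinal, and section 2.9 describes none.

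It also stands that the size is assumption-driven, that it is in SD units whereas the first primary outcome is a proportion, and that with an endpoint at Month 3 no interim visit would precede it.

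Three stronger readings are tempting but not supported:

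- **The interim data go unused.** Section 2.1 and the Discussion both say that they will be analysed. What is missing is a method in section 2.9.
- **Dropouts are counted as non-adopters.** Section 2.8.1.1 defines the proportion by "dividing the number of individuals exceeding this threshold by the total number of participants". An intention-to-treat set with imputed status satisfies that wording, and no rule scores dropouts as failures.
- **Imputation in the per-protocol set is incoherent.** That set is defined so that "only participants who complete the intervention and follow-up will be included in a per-protocol (PP) analysis". Completers can still miss an item, a questionnaire or an interim visit.

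**Conclusion.** The point holds in a limited form. Section 2.9 names a weaker predictor set than the trial will have collected, under an assumption that those omitted scores would make more credible. It also leaves the endpoint undated and does not carry through the longitudinal analysis promised in the Discussion.

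The possible bias is about 0.02 to 0.17 SD, well under one standard error at this sample size. It requires an endpoint later than Month 3 and dropout that depends on interim scores differently by arm. A reader might infer that the primary result will be biased; the documents do not support that, because they say nothing about how dropout will arise. The precision loss does not depend on differential dropout, but it is modest. The change is worth making because it is cheap and the data will already exist.

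**What to change.** In section 2.9:

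1. State the endpoint month.
2. Use one imputation model with arm as a predictor, containing baseline and the observed Month 3, 6 and 9 behaviour and knowledge scores. Keep the predictor set small. With about 29 per arm, and about 23 completers, separate models by arm would be hard to support.
3. Impute the scores, then derive adopter status from the imputed scores.
4. Specify the promised longitudinal analysis as a mixed model or GEE over all visits, with arm, visit, arm-by-visit interaction and baseline score.

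The cost is wording and slightly more programming, plus some model instability at this sample size. No new data are needed.
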